Prospective study on the effects of adalimumab treatment in patients with rheumatoid arthritis who are naïve for TNF- blocking therapy and patients who do not respond (anymore) to prior treatment with other anti-TNF- medication.

Protocol version 2.1

04-02--2008

[name]

[name]

[name]

[name], PhD

Division of Clinical Immunology and Rheumatology, F4-218

Department of Medicine,

Academic Medical Center/University of Amsterdam

[name]

[contact] [contact] E-mail:[contact]

| *Schedule of Observations* |  | Screening | T=-2 | T=0 | T=4 | T=16 | T=28 | T=40 | T=52 |
| --- | --- | --- | --- | --- | --- | --- | --- | --- | --- |
| *Visit number* |  | **V0** | **V1** | **V2** | **V3** | V4 | **V5** | **V6** | **V7** |
| TNO/insurance request for approval | *(DAS 28)* | X |  |  |  | X |  |  |  |
| Demographics | *Age*  *Race*  *Height*  *Weight*  *Alcohol*  *Smoking* |  | X |  |  |  |  |  |  |
|
| DMARD & biological history | *DMARDs*  *Prednison*  *Biologicals* |  | X |  |  |  |  |  |  |
| Concommitant. medication |  | X | X | X | X | X | X | X | X |
| In- and exclusioncriteria |  | X | X |  |  |  |  |  |  |
| Informed consent |  |  | X |  |  |  |  |  |  |
| mRNA for storage |  |  |  | X | X | X | X | X | X |
| DNA sample (genetic polymorphisms) |  |  |  | X |  |  |  |  |  |
| X-thorax (< 3 mnd voor baseline) |  |  | X |  |  |  |  |  |  |
| PPD (<6 mnd voor baseline) |  |  | X |  |  |  |  |  |  |
| Virology screening | *Hepatitis B, C, HIV* |  | X |  |  |  |  |  |  |
| Urine -HCG | *pregnancy test* |  | X |  |  |  |  |  |  |
| IgM RF, anti- CCP, ANA, ds-DNA |  |  | X |  |  |  | X |  | X |
| Radiological progression | *Sharp modified by*  *Van der Heijde score* |  |  | X (<3mnd accepted) |  |  |  |  | X |
| (X-hands, feet) |
| Routine laboratory testing | *ESR, CRP, Hb, Ht, Leuco’s, Trombo’s, creatinin, ureum, Na, K, ALAT (SBPT), ASAT (SGOT), LDH, Gt, AF, glucose, bilirubine, alkaline phosphatase, protein and albumin,* |  | X | X | X | X | X | X | X |
| *Urine dipstick: glucose, protein, blood* |

| *Schedule of Observations* |  | Screening | T=-2 | T=0 | T=4 | T=16 | T=28 | T=40 | T=52 |
| --- | --- | --- | --- | --- | --- | --- | --- | --- | --- |
| *Visit number* |  | **V0** | **V1** | **V2** | **V3** | **V4** | **V5** | **V6** | **V7** |
| Disease activity | *DAS 28*  *ACR*  *RADAI*  *HAQ-score*  *VAS pain*  *VAS dis.act*  *Dis act Phys/observer*  *Dis act Pat*  *Morning stiffness*  *Short form health survey (SF 36)* |  |  | X | X | X | X | X | X |
| Bonemineraldensity | *DEXA-scan* |  |  | X |  |  |  |  | X |
| Serum for storage | *serologic markers, anti-antibodies, markers of boneformation & resorption* |  | X | X | X | X | X | X | X |
| Urine for storage | *markers for boneresorption & cartilage degradation* |  | X | X | X | X | X | X | X |
| Vital signs | *BP, pulse, temperature (oraal), weight, height* |  | X | X | X | X | X | X | X |
| Employement status | *jobstatus, sickleave, work resumation, % work* |  |  | X |  | X |  |  | X |
| Safety checks | *Infection , malignancy, hospital admittance, adverse events* |  |  | X | X | X | X | X | X |

Table of contents

[1. Introduction. 4](#__RefHeading___Toc60568766)

[Targeted therapy by TNF- blockade in RA. 4](#__RefHeading___Toc60568767)

[Objectives 6](#__RefHeading___Toc60568768)

[Research question(s) 6](#__RefHeading___Toc60568769)

[2. Investigational Plan 7](#__RefHeading___Toc60568770)

[Study medication and dosage 7](#__RefHeading___Toc60568771)

[Design. 7](#__RefHeading___Toc60568772)

[Duration of study 8](#__RefHeading___Toc60568773)

[Inclusion criteria: 8](#__RefHeading___Toc60568774)

[Exclusion criteria: 9](#__RefHeading___Toc60568775)

[Screenings procedures 10](#__RefHeading___Toc60568776)

[Variables and schedule of observations 10](#__RefHeading___Toc60568777)

[Background information 10](#__RefHeading___Toc60568778)

[Primary endpoint 11](#__RefHeading___Toc60568779)

[Secondary endpoints 11](#__RefHeading___Toc60568780)

[**Safety Variables** 12](#__RefHeading___Toc60568781)

[Adverse events 12](#__RefHeading___Toc60568782)

[**Laboratory variables** 12](#__RefHeading___Toc60568783)

[**Additional variables** 13](#__RefHeading___Toc60568784)

[**Clinical variables** 13](#__RefHeading___Toc60568785)

[Concomitant illnesses 14](#__RefHeading___Toc60568786)

[Concomitant treatment 14](#__RefHeading___Toc60568787)

[Concomitant medications 15](#__RefHeading___Toc60568788)

[Infections 16](#__RefHeading___Toc60568789)

[Pregnancy 16](#__RefHeading___Toc60568790)

[Overdosage 16](#__RefHeading___Toc60568791)

[Adverse events 17](#__RefHeading___Toc60568792)

[*Definition of serious and non-serious adverse events* 18](#__RefHeading___Toc60568793)

# 1. Introduction.

Although the etiology of rheumatoid arthritis (RA) remains elusive, immune-mediated mechanisms are likely of crucial importance. The evidence to support a role of CD4+ T-cells in the immune response in RA patients is substantial, although circumstantial. It has become clear that cells other than lymphocytes, in particular activated macrophages, play a critical role as effector cells in chronic disease (1). These cells are highly activated and secrete a variety of cytokines as well as matrix metalloproteinases. The macrophages often constitute the majority of the inflammatory cells in the synovial sublining (2). The importance of these cells and their soluble mediators is supported by clinical observations. Local disease activity is particularly associated with the number of macrophages and the expression of cytokines, such as TNF- and IL-6, in synovial tissue (3). There is also a significant positive correlation between intimal lining layer depth and cell counts for macrophages in the synovial sublining on the one hand and radiographic signs of joint destruction after follow-up on the other (4). The pivotal role of TNF- - at least in the majority of RA patients - has been confirmed by the impressive effects of specific therapeutic strategies targeting the TNF- molecule (5-9).

## Targeted therapy by TNF- blockade in RA.

Therapy with TNF- blockade plus methotrexate may provide sustained clinical benefit in patients with active RA despite previous therapy with methotrexate. This combined therapy may not only control the symptoms and signs of RA effectively, but may also improve the quality of life (7). Therapy with the chimeric monoclonal antibody infliximab plus methotrexate prevents progressive joint damage and results in improvement in radiographic scores of joint damage in a significant percentage of patients. The combination of infliximab and methotrexate could halt the progression of joint damage not only in patients with limited joint damage, but also in those with extensive damage, whereas conventional therapies only have a moderate effect on progression of the disease. Still, at least 30% of the patients do not respond to infliximab therapy with regard to arthritis activity (5;7). One of the explanations could be that patients develop anti-infliximab antibodies (human anti-chimeric antibodies, HACA’s) after initiation of treatment. Consistent with this notion we have recently shown that the formation of such antibodies may lead to infusion related allergic reactions (10) and lack of clinical response (14). The inhibitory antibodies are of IgG1 and IgG4 subclasses (unpublished data). The observed class switched B cell response points to a T cell dependent humoral response. Therefore there can be specific T helper epitopes in the adalimumab sequence against which T cel reactivity may be induced.

This can give insight in the T cell response involved in antibody formation against the anti-TNFα therapeutic antibodies. This will allow either modification of the therapeutic antibodies to prevent inhibitory antibody formation or patient monitoring at the start and during treatment.

Adalimumab is a novel recombinant human IgG1 monoclonal antibody specific for human TNF-α. Adalimumab was created using phage display technology resulting in an antibody with human derived heavy and light chain variable regions and human IgG1:К constant regions. Adalimumab is produced by recombinant DNA technology in a mammalian cell expression system and is purified by a process that includes specific viral inactivation and removal steps. It consists of 1330 amino acids and

has a molecular weight of approximately 148 kilodaltons. Adalimumab has been approved by the FDA and EMEA and is now available in the Netherlands *(for detailed information see appendix).*

We have treated RA patients with adalimumab as part of our routine clinical practice; these patients did not fulfill the Eular response criteria (DAS 28) for clinical improvement after infliximab treatment. Of importance, the majority of these patients do respond to adalimumab treatment. Conceivably, some of these patients have developed human anti-chimeric antibodies, which affect infliximab treatment, but not adalimumab treatment.

The goal of this study is to follow up patients who will initiate adalimumab as their first TNF- blocking biological treatment and patients who initiate adalimumab after they failed other TNF- blockers. We will look for clinical parameters and serological markers that may differentiate responders from non-responders on adalimumab. We will evaluate changes in disease activity in relationship to adalimumab treatment by monitoring both clinical signs of arthritis activity and markers of bone and cartilage destruction. Furthermore we will measure antibodies formed against prior TNF- blockers before initiating adalimumab in patients who failed prior anti-TNF- treatment. This will allow us to determine the role of anti-antibody formation in the response to TNF- blockade. In addition, in an exploratory setting we will collect biological data to study the effects of factors other than anti-antibody formation that could affect the clinical response. Conceivably, a subset of patients has disease primarily driven by cytokines other than TNF-. The minority of patients who fail both the prior TNF- blocker, and adalimumab might fit in this category and we will try to identify the driving immunological mechanisms in these patients.

## Objectives

To evaluate the response to adalimumab treatment in TNF- blockade naïve patients and patients who failed prior other anti-TNF- treatment and to understand the mechanisms underlying the clinical response to TNF- blockade.

Research question(s)

1. *What factors distinguish responding patients from non responding patients on adalimumab treatment? (anti-(anti-TNF-**) antibody formation, differences in cytokine profiles or other serological markers, RA activity driven by other mediators than TNF-**)*

2) What percentage of patients (TNF- blockade naïve versus failures on prior anti-TNF- treatment) respond after 16 weeks of adalimumab treatment?

*3) What is the clinical efficacy of adalimumab after 1 year treatment?*

*(Eular response criteria (DAS 28), ACR response, RADAI, SF 36, HAQ, and radiological progession)*

*4) Can we find genetic markers, e.g. genetic polymorphisms in the TNF-* *genes, that may predict diagnosis, efficacy and side-effects of treatment in the individual patient?*

*5) Can periferal blood (mRNA) micro-array analysis identify new markers that distinguish responders from non-responders to adalimumab treatment?*

*6) What are the effects of adalimumab on bonemineraldensity (DEXA) and bone metabolism (serum and urine markers for boneformation and resorption)?*

*7) What are the effects of adalimumab on functioning at work and sickleave?*

*8)* *Are inhibitory antibodies formed in a T cell dependent humoral response and if so, which are the specific epitopes in the adalimumab sequence recognized by T cells involved in antibody formation against itself?*

#

# 2. Investigational Plan

## Study medication and dosage

**Generic name: adalimumab**

**Trade name: Humira®**

Dosage: 40 mg (0,8 ml) by subcutaneous injection at baseline and every other week.

After succesfull training of the injection technique at the out-patient clinic under supervision of a special trained nurse or physician, patients are allowed to administer adalimumab at home.

There will be a ± 7-day deviation for all return visits.

All visits will be fixed with reference to the baseline visit.

The study medication will be on prescription (according to the guidelines of “de Nederlandse Vereniging voor Reumatologie” and the manufacturer’s instructions).

## Design.

A monocenter prospective, exploratory study with a 1 to 2-week screening period and a 52-week follow-up period in 120 RA patients who receive adalimumab treatment in routine rheumatological practice and are TNF- blockade naïve or have failed to (or no longer) respond to other anti-TNF- treatment. There is no group of patients receiving control treatment, since it is considered unethical to withhold active treatment for 52 weeks in patients with active RA. Previous work has shown the efficacy of adalimumab in randomized trials (8;9).

The goal of the present study is to evaluate the response to adalimumab treatment in the TNF- blockade naïve patients and patients who failed on other prior TNF- blocking treatment. Therefore, responders will be compared with non-responders after all included patients have received anti-TNF- therapy in the form of adalimumab. Furthermore the goal is to understand more of the mechanisms underlying the response to anti-TNF- treatment. Adalimumab treatment will be discontinued in patients who do not fulfill the Eular response criteria for improvement (DAS 28) at week 16, according to routine clinical practice.

Patients who discontinue adalimumab at or after week 16 for lack of respons or other reasons will get a final clinical assessment as part of the close out visit. The reason for discontinuation will be noted in the case record form. These patients will not be followed for measurement of clinical parameters. In patients who respond, treatment will be continued and may be extended after the 52-week follow-up period of this study. Patients will be included starting January 2004.

Patients who drop out of the study before week 16 for any reason will be replaced by new patients, the reason of discontiuation will be noted in the case record form (*see withdrawl and replacement of patients)*

## Duration of study

All patients participating in this study will receive 40 mg (0,8ml) adalimumab by subcutaneous injection every other week after fulfilling all inclusion criteria at baseline. All patients must have approval for reimbursement for TNF-blockade by their insurance company (DAS 28 >3.2). Patients will be seen during the study for efficacy and safety assessments at weeks 4, 16, 28, 40 and 52 using validated and generally accepted evaluation criteria (see laboratory and clinical variables). All visits will be fixed with reference to the baseline visit. Evaluation of ACR 20 and Eular response (DAS 28) will be performed at 16 weeks after initiation of adalimumab. The final clinical assessments will be performed at 52 weeks. If the patient does not meet the Eular criteria for moderate or good response at 16 weeks, adalimumab treatment is discontinued and no further assessments will be done.

Inclusion criteria:

1) Patients with the diagnosis rheumatoid arthritis according to the American Rheumatism Association (ARA) 1987 criteria and in ACR 1991 functional classes I, II, and III *(see appendix)*

2) The patient is naïve for anti-TNF- therapy or has failed other prior TNF- blockers

3) DAS 28  3.2

4) Age > 18 and  85 years old

5) Use concurrent methotrexate treatment (5 - 30 mg/week; stable since at least 28

days before initiation) during the study. Subjects may be taking nonsteroidal anti-

inflammatory drugs, provided the dose and frequency have been stable for at

least 28 days. Subjects may be receiving prednisone therapy  10 mg/day

provided that the dosage has been stable for at least 2 months prior to entry.

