### Secondary endpoints

The secundary endpoint of the study is the proportion of patients with a 20%, 50%, and 70% clinical improvement according to the ACR response criteria (11) at 4, 16, 28, 40 and 52 weeks after the initiation of adalimumab treatment. The parameters of disease activity e.g. tender joint count, swollen joint count, patient’s assessment of pain, patient’s global assessment, investigators global assessment, duration of morning stiffness, health assessment questionnaire, DAS 28, SF-36 (short form health survey) and RADAI (12) will be assessed at each time point starting from baseline. Also an assessment of the influence of adalimumab treatment on physical and mental wellbeing in relation to employment status, job-satisfaction and sickleave will be implemented in the form of questionnaires.

In addition we will look at the influence of adalimumab on bonemineraldensity, bonemetabolism.

This will be done by analysing serum and urine markers for bone formation and resorption, performing a DEXA scan before- and one year after adalimumab initiation.

We will look for genetic markers, e.g. genetic polymorphisms in TNF- genes, that may predict diagnosis, efficacy and side-effects of treatment in the individual patient.

In the future micro-array analysis may be done to screen for new markers that distinguish responders from non-responders. Also, immunological responses raised against adalimumab antibodies will be researched, comprising antibody formation and T cell responses.

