### Withdrawl and replacement of patients

Patients who drop out of the study before week 16 for any reason will be replaced by new patients, the reason of discontiuation will be noted in the case record form.

These patients will be seen for a final clinical assessment as part of the close out visit.

This visit will include physical examination, final assessment of disease activity (ACR, DAS 28, RADAI, SF 36), follow up of previous adverse events. Blood will be drawn for safety screening of clinical heamatology and chemistry parameters. Furthermore final immuno- serology to screen for auto-antibody formation (ANA, anti-ds DNA). Titers of IgM-RF and anti-CCP will also be drawn at this visit.

Premature discontinuation of study

The investigator has the right to discontinue this study at any time for medical and/or administrative reasons. As far as possible, this should occur after mutual consultation. Furthermore adalimumab treatment will be discontinued if there is no reimbursement by the insurance company.

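### After week 16 only patients still responding and treated are measured, so one-year proportions will overstate efficacy in the treated cohort unless stopped patients stay in the denominator

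*Protocol*

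**What the plan says.** Two passages in section 2 of the protocol limit data collection after week 16. Under Duration of study, if a patient lacks a moderate or good EULAR response "at 16 weeks, adalimumab treatment is discontinued and no further assessments will be done". The Design section covers everyone who discontinues at or after week 16, for lack of response or any other reason. They "will get a final clinical assessment as part of the close out visit", the reason is recorded, and then: "These patients will not be followed for measurement of clinical parameters".

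The questions asked are wider. Research question 3 reads "What is the clinical efficacy of adalimumab after 1 year treatment" and names EULAR and ACR response, RADAI, SF-36, HAQ and radiological progression. The secondary endpoint is the "proportion of patients with a 20%, 50%, and 70% clinical improvement according to the ACR response criteria", assessed "at 4, 16, 28, 40 and 52 weeks after the initiation of adalimumab treatment". Neither is limited to week-16 responders.

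The Data analysis section plans descriptive proportions and logistic regression. It gives no denominator for the late visits and does not say how discontinued patients are counted. Drop-outs before week 16 are replaced, whatever the reason (Design; Withdrawal and replacement of patients).

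**The concern.** The protocol defines a single ACR series from week 4 to week 52, but the patients behind it change at week 16. Up to then, EULAR non-responders are included. From week 28 the only patients with data are those who passed a response filter and stayed on treatment.

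The filter may continue to act after week 16. The Primary endpoint section ties continued reimbursement to a DAS 28 fall of at least 1.2, and the section on premature discontinuation stops treatment without reimbursement. Patients who lose response can then leave because of the outcome being measured.

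If late proportions are taken among those still followed, the series can rise at week 28 although no patient has improved, and the one-year figure describes retained responders. The outcomes that are not simple responder counts have a further problem: for stopped patients no week-52 value exists.

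**Working it through.** **Plan's own figure.** The Design section gives "52-week follow-up period in 120 RA patients" with no expected response rate, precision or power, so there is nothing to reproduce. N = 120 is taken as given.

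**Inputs.** The protocol gives no response or retention rate for adalimumab. Its only related figure is at least 30% non-response to infliximab (Introduction), used here only to centre a range. All of the following are assumptions:
- R, week-16 EULAR response: 0.5 to 0.8, centre 0.7
- q, later ACR20 among patients still followed: 0.6 to 0.8, centre 0.7
- d, loss between week 16 and the later visit: 0 or 0.15
- s, ACR20 rate in week-16 non-responders: 0 to 0.3

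**Step 1: two denominators.**
Among those followed, the proportion is q. Among all 120, with stopped patients counted as non-responders, it is q × R × (1 − d).
- Centre, d = 0: 120 × 0.7 = 84 patients followed; 0.7 × 84 = 58.8 responders; 58.8/120 = 49.0%. Gap 70.0 − 49.0 = 21.0 points.
- Smallest gap, R = 0.8, q = 0.6: 0.60 − 0.48 = 12 points, with 96 followed.
- Largest gap, R = 0.5, q = 0.8: 0.80 − 0.40 = 40 points, with 60 followed.

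**Step 2: later loss of 15%.** At the centre, 84 × 0.85 ≈ 71 patients; 0.7 × 71/120 = 41.4%; gap 28.6 points. Over the same ranges of R and q the gap is 19 to 46 points.

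**Step 3: if some stopped patients would have responded later.** The gap is (1 − R) × (q − s). At R = q = 0.7 this is 0.3 × (0.7 − s): 18, 15 and 12 points for s = 0.1, 0.2 and 0.3. It reaches zero only at s = 0.7, where stopped patients would do as well as retained ones.

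**Step 4: an apparent rise without change.** Suppose ACR20 at week 16 is 70% in EULAR responders and 10% in non-responders. The week-16 proportion is 0.7 × 0.7 + 0.3 × 0.1 = 52%. If no patient changes, the proportion among those followed at week 28 is 70%.

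**Step 5: replaced drop-outs.** If 5%, 10% or 15% of those enrolled drop out before week 16 and are replaced, enrolment is 120/0.95 = 126.3, 120/0.90 = 133.3 or 120/0.85 = 141.2. The 58.8 responders are then 46.5%, 44.1% or 41.6% of all enrolled.

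**Step 6: outcomes with no value to impute.** After baseline, X-rays and DEXA are scheduled only at week 52, and the close-out visit lists neither. HAQ, SF-36, RADAI and work status may exist up to week 16 or close-out, but not at week 52 for a stopped patient. Counting such a patient as a failure settles a binary endpoint. It does not supply a radiographic score or a bone density.

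**The case against.** The strongest reply is that the protocol nowhere prescribes an analysis of observed patients only. A reader might infer that the late proportions as planned are overstated. The documents do not support that: no denominator is fixed, and if all starters are used with stopped patients as non-responders, the overstatement due to the stopping rule is zero. Denominators are often left to an analysis plan, which is not at hand. This stands, and the claim about ACR proportions is therefore conditional.

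A reader might also contrast clean early visits with selected late ones. That goes too far as well. Replacement of early drop-outs means the planned 120 at week 16 are already selected for having stayed.

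The close-out assessment and the recorded reason for stopping provide information for classifying stopped patients. The visit content, set out for earlier drop-outs, includes ACR and DAS 28. Question 3 can also be read as asking about patients treated for a full year, which is a legitimate quantity if labelled so. Finally, every rate in the illustration is assumed, including the 70% later ACR20.

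These replies do not dispose of the point. The collection rule is fixed in the protocol, the one-year questions are not restricted to match it, and an analysis plan cannot recover week-52 values that were never collected.

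**Conclusion.** The mismatch is real. As written, data at weeks 28, 40 and 52 can come only from patients who responded at week 16 and remained on treatment, while the one-year objectives are posed without that limit. Proportions among those followed will overstate efficacy in the treated cohort unless stopped patients stay in the denominator. The direction requires only that stopped patients would do worse than retained ones. The size rests wholly on assumed rates.

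Severity is moderate. The study is exploratory with no control group, the affected endpoints are secondary and descriptive, and this rule does not touch the week-16 primary response rate.

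**What to change.** - For ACR 20/50/70 and EULAR response at weeks 28, 40 and 52, take as denominator every patient who started adalimumab, including those replaced. Count anyone who has stopped as a non-responder from that visit on.
- Report the proportion among patients still on adalimumab second, labelled as such.
- Label week-52 X-ray, DEXA, HAQ, SF-36, RADAI and work results as conditional on week-16 response and continued treatment. Do not present them as the effect in the whole cohort.
- Reconcile the Duration of study statement that assessments cease with the close-out assessment in Design. Also reconcile the EULAR continuation criterion with the reimbursement threshold in the Primary endpoint section, since a moderate response can involve a DAS 28 fall below that threshold.

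This needs no new visits and leaves the treatment-stopping rule as it is. The cost is that reported one-year proportions will be lower, and the radiographic, bone and work results will carry a narrower claim.
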